### Laboratory analysis

Blood samples will be drawn for complete blood count, glycaemic metabolism (glucose and HbA1c), lipid panel (HDL-C, LDL-C, total cholesterol, triglycerides, lipoprotein A, apo B, apoA), thyroid function, ferritin and inflammation parameters (hs-CRP, leucocyte volume). Full hormonal profile will be analyzed making sure that premenopausal women are in the first 9 days of their menstrual cycle [estradiol, follitropin (FSH), lutropin (LH), sex hormone binding globulin (SHBG), free and total testosterone, dehydro-epiandrosterone sulfate (DHEAS), free androgen index (FAI), anti-Mullerian hormone].

Blood samples will also be processed and stored at −80°C for high-throughput “omics” analysis and biobanking by qualified personnel at CNIC. For epigenetics, DNA from the blood samples will be extracted using Infinium Methylation EPIC arrays, which include over 450.000 DNA bases and identify positions and regions hyper and hypomethylated for each time point to estimate the biological age using the getClock R package.

For lipidomics, plasma samples will be diluted with acidified methanol and lipids will be extracted with methyl-tert-butylether (MTBE) (30). Internal standard mixture containing Splash Lipidomix Mass Spec Standard and Ceramide C17 (d18:1/17:0) (Avanti Polar Lipids) will be added to the samples for quantification purposes. Organic phase will be dried-out, resuspended in appropriate solution and infused via nanoflow ESI source (Advion Triversa Nanomate) into a Quadrupole-Orbitrap Hybrid mass spectrometer (QExactive, Thermo Fisher Scientific). Data will be processed using LipidXplorer software (31).

### Vascular imaging protocol

Vascular ultrasound imaging will be carried out using Philips EPIQ Elite 7.0.5 and the protocol includes 2D VUS of the carotid, aorto-iliac and femoral territories (cross-sectional and longitudinal images) and 3D VUS of any plaque (volume set) with an approximate examination time of 40 min (Figure 2). Imaging analysis will include plaque presence, thickness, volume and degree of stenosis (5). Strain-rate measurements of the carotid cross-sectional image will also be assessed to increase our understanding of the elastic properties and function of the arterial walls providing potential information on arterial health status by analyzing distensibility/compliance coefficients, b-stiffness index, circumferential strain/strain rate, peak radial velocity (Figure 3) (32).

**Figure 2 F2:**
[figure not shown]
2D and 3D vascular ultrasound **(A)** 2D images of femoral artery showing atherosclerotic plaque (arrow) located in the common femoral artery prior to bifurcation. **(B)** 3D images of carotid artery bifurcation showing atherosclerotic plaque (arrow head) located in internal carotid artery.

**Figure 3 F3:**
[figure not shown]
Carotid arterial strain curves with different colors representing the four arterial segments included in strain analysis the white line represents average radial strain.

### Follow-up and end-points

At 6-month follow-up, participants will be contacted by telephone or email to undergo similar testing as baseline, except vascular imaging. The primary endpoint will be changes from baseline Fuster BEWAT score (FBS) which has shown a strong inverse association with subclinical atherosclerosis (24). FBS will enable the monitoring of global changes in healthy behaviors and non-laboratory-based CV health factors. The FBS measures CV risk exclusively on the basis of the easily measurable predictors blood pressure [B], exercise [E], weight [W], alimentation [A], and tobacco smoking [T], and is thus a highly relevant outcome given the characteristics of our study population. Secondary outcomes will include changes in overall knowledge, attitudes, and physical activity, diet, smoking, cholesterol, glucose, blood pressure, weight, and self-rated family health. We expected that women who underwent imaging will improve their CV lifestyle in a better way than women who do not undergo imaging because they will be witnesses of their own vascular damage, and thus, the FBS will score higher in the imaging group. Similar procedures will be carried out on the 12-month visit to evaluate long-term effects. CV events will be also registered in all follow up visitsfor participants with plaques, and also for those without plaques, as well as data regarding the approach taken by the participant inquiring whether she has any new medical treatment, has seen a healthcare professional with her results or if additional testing has been ordered based on blood tests or vascular imaging results.

### Statistical analysis

Preliminary descriptive statistical analysis (boxplots, histograms, univariate parametric and non-parametric tests) will be used once significant amounts of data have been collected. All parameters to be collected are summarized in Table 2. We will evaluate lifestyle changes by the FBS using multivariate logistic regression. The dependent variable will be the improvement or worsening of the score between baseline and follow-up, and the analysis will be adjusted for covariates such as age to identify groups of women potentially more impacted by the imaging-based strategy. Additionally, machine learning techniques will be derived to acquire knowledge from the data. In particular, supervised and semi-supervised classifiers will be trained with 80% of the data to derive risk prediction models. Remaining 20% of the data will serve as a validation cohort. Also, clustering analysis will be performed in order to observe phenotype groups in our patients that explain the clinical variance for sample size calculation, the following formula was applied:$$n=\frac{{\left(Z_{\alpha /2}+Z_{\beta }\right)}^{2}\cdot (\;p_{1}\cdot (1-p_{1})+p_{2}\cdot (1-p_{2}))}{{\left(\;p_{1}-p_{2}\right)}^{2}}$$

**Table 2 T2:** WAKE UP study variables.

Questionnaires	
- CV risk perception	health problems, personal health conditions, CV risk and general knowledge regarding CV disease in women
- CV risk factors	smoking, hypertension, dyslipidaemia, diabetes, obesity, poor diet, physical inactivity, family history CVD, metabolic syndrome, systemic autoimmune collagen-vascular disease, preeclampsia or gestational diabetes
- Non-CV disease	Thyroid disorders, chronic renal failure, pulmonary disease, hepatic disease, cancer, autoimmune disease
- CV risk scores	FBS, SCORE, SCORE 2, ASCV, FHS 10, FHS 30
- Smoking	Age of initiation, n° of cigarettes per day, exposure to secondary smoking
- Physical activity	Hours sitting on a workday, time spent walking on a workday, practice of moderate and/or intense exercise
- Diet	Portions of carbohydrates, proteins, fruits and vegetables, dairy products, sweets, fat, water and alcohol
-Reproductive factors	Age of menarche, contraceptive use and type, complications during pregnancy, age of menopause
-Psychosocial factors	Education level, employment status, marital status, stress scale, emotional state scale
-Family health (first-degree relatives)	Perception of family lifestyle, diet, exercise. Family history of CV risk factors, cancer, hepatic disease, thromboembolic disease
- Sleep	Sleep disorders (apnea, insomnia, restless legs syndrome, etc.) hours of sleep per night, difficulties in falling asleep or awakenings during the night
Anthropometric measurements	
Blood pressure, weight, height, BMI, waist circumference and body composition	
Biochemistry	
Glycemic metabolism	Glucose and HbA1c
Lipid panel	HDL-C, LDL-C, total cholesterol, triglycerides, lipoprotein A, apo B, apo A
Thyroid function	TSH, T4
Inflammatory parameters	hs-CRP, leucocytes volume, ferritin, albuminuria (urine sample)
Hormonal profile	Estradiol, follitropin [FSH], lutropin [LH], sex hormone binding globulin [SHBG], free and total testosterone, dehydro-epiandrosterone sulfate [DHEAS], free androgen index [FAI], anti-Mullerian hormone
Omics	
Lipidomic profile	Glycerophosphocholines, glycerophosphoethanolamines, glycerophosphoserines, glycerophosphoglycerols, glycerophosphoinositols, glycerophosphates and respective lysolipids; ceramides and sphingomyelins; diglycerides and triglycerides
Vascular ultrasound	
2D ultrasound: Carotid, aorto-iliac and femoral territories.	Plaque presence, no. of plaques, thickness of plaques, length of plaques and degree of stenosis
3D ultrasound: Carotid and femoral	Plaque volume and grey scale for composition
Vascular strain: Carotid cross-sectional image.	Distensibility/compliance coefficients, b-stiffness index, circumferential strain/strain rate, peak radial velocity

CV, cardiovascular; FBS, Fuster BEWAT score; SCORE, Systemic Coronary Risk Estimation; ASCV, Atherosclerotic CV disease; FHS, Framingham risk score.

*Z_α_*_/2_ and *Z_β_* are the critical values for the chosen significance level and power (splitting the significance level evenly between tails); *p*1 is the proportion of individuals who develop the disease without treatment, 45% according to the PESA study. *p*2 is the proportion of individuals who develop the disease with treatment, assuming 54% of our individuals will follow the provided recommendations to reduce the CVFR probability. With this setup, *n* = 481 patients will report a statistical power 1−*β* of 80% and significance level *α* of 95%, which are satisfactory in terms of clinical purposes. Given our previous experience with lifestyle intervention programs, we are well powered to detect relevant changes in the imaging group. Larger effects are anticipated in individuals with plaques, as there is more room for improvement. To account for potential variability introduced by including women across a wide age range, we will stratify participants into predefined age groups (e.g., young: 40–50 years: adult: 50–60 years, elderly: 60–70 years) during analysis. Additionally, we will apply multivariable regression models adjusted for age as a continuous variable to control for age-related confounding factors. This approach ensures that the impact of age on the progression of the atherosclerotic process is appropriately considered and mitigates the risk of contamination of information between age groups.

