## Methods

### Study design and population

WAKE UP is a longitudinal, prospective, case-control study that will include 720 women aged 40–70 years-old (from pre- to post-menopause) with at least one CV RF, defined as cigarette smoking, hypertension, dyslipidaemia, diabetes, obesity, poor diet, physical inactivity, family history of premature CV disease, metabolic syndrome, systemic autoimmune collagen-vascular disease, history of premature menopause, gestational diabetes or hypertensive disorders of pregnancy according to prevention guidelines for women (17). Exclusion criteria include any prior history of CV disease (myocardial infarction, angina pectoris, arrythmias, stroke, peripheral vascular disease, angioplasty, valvular heart disease, congenital heart disease or heart surgery), pregnancy and refusal to sign informed consent.

The study will include baseline, 6-month and 12-month follow-up visits (Figure 1). All visits will include traditional and non-traditional risk assessment, blood sampling and omics analysis (Table 1). Vascular imaging studies will be only performed at baseline, after randomization 1:1 for imaging risk assessment, 360 with VUS vs. 360 age- and RF-matched controls without imaging. Participants in the imaging group will be informed about their personalized CV risk based on imaging results and will be given lifestyle recommendations accordingly. Women with atherosclerotic plaque will be shown their arterial images and will be explained the meaning and CV risk associated with these findings. Those without plaques will be shown example images of atherosclerotic plaque and similar explanations will be given.

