Several scores will be calculated to assess CV risk: Fuster BEWAT score (FBS) (24) compiles 5 variables (blood pressure, exercise, weight, alimentation, and tobacco) into a 15-point ordinal scale. For each variable, a numeric grading system (0, 1, 2, or 3) has been adopted in relation to international guidelines, being 3 the optimal value. Systemic Coronary Risk Estimation (SCORE) algorithm will be used to estimate risk of fatal CV disease by gender, age, systolic blood pressure, total cholesterol and smoking status (25). SCORE2 is an update of the original SCORE algorithm derived, calibrated, and validated to predict 10-year risk of first-onset CV disease by enhancing the identification of individuals at higher risk of developing CV disease across Europe (26). Atherosclerotic CV disease (ASCVD), based on age- and sex-specific pooled cohort equations estimates 10-year risk of nonfatal myocardial infarction, coronary heart disease death, or stroke for asymptomatic adults 40–75 years of age (27). Ten- and 30-year Framingham Risk Scores (28, 29) predict risk of hard coronary heart disease (coronary death, myocardial infarction, stroke).

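### The primary endpoint, change in the 15-point FBS, is analysed only as improved or worsened: size of change is lost, unchanged scores have no category, and baseline FBS is not named as a covariate

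*Protocol article*

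**What the plan says.** - **Endpoint.** Under Follow-up and end-points: "The primary endpoint will be changes from baseline Fuster BEWAT score (FBS"). The same section expects the imaging group to improve its lifestyle more and so to have the higher FBS.
- **Scale.** Under Clinical data collection and risk scores, five items graded 0 to 3 are combined "into a 15-point ordinal scale". The total is an integer from 0 to 15, so a change of zero is possible.
- **Model.** Under Statistical analysis: "We will evaluate lifestyle changes by the FBS using multivariate logistic regression". The next sentence defines the outcome: "The dependent variable will be the improvement or worsening of the score between baseline and follow-up".
- **Covariates.** That sentence goes on: "the analysis will be adjusted for covariates such as age to identify groups of women potentially more impacted by the imaging-based strategy". Later in the section: "we will apply multivariable regression models adjusted for age as a continuous variable". Age is the only covariate named. Baseline FBS is neither named nor excluded.
- **Other analyses of FBS.** None is stated for inference. The parametric and non-parametric tests at the start of the section are described as preliminary and descriptive.
- **Arms.** Under Study design and population: "360 with VUS vs. 360 age- and RF-matched controls without imaging".

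**The concern.** The endpoint is a change on a 16-value integer scale, and the stated analysis reduces it to its sign. Three consequences follow.

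1. **Size is lost.** A gain of one point and a gain of six count the same. The resulting odds ratio describes who moved up. It does not say how much higher the imaging group scores, which is what the stated expectation concerns.
2. **Two categories do not cover three outcomes.** A woman with an unchanged score has neither improved nor worsened. Dropping such women selects on an outcome measured after randomisation. Pooling them with either group changes what is estimated. With the rule open, it could be chosen after the data are seen.
3. **The starting score matters.** A woman near 15 has little room to improve and a woman near 0 little room to worsen, so the chance of improving depends on baseline FBS. Adjusting for it would also sharpen the comparison of arms.

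At stake is power for the primary comparison and a primary result that cannot be read in FBS points.

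**Working it through.** **1. The article's own figure.** The sample-size formula with p1 = 0.45, p2 = 0.54, two-sided α = 0.05 and 80% power gives

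n = (1.960 + 0.842)² × (0.45×0.55 + 0.54×0.46) / 0.09² = 7.849 × 0.4959 / 0.0081 = 480.5, rounded to 481 per arm.

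This reproduces the printed 481. The first proportion is "45% according to the PESA study" and is described as developing disease. The second is the share expected to follow the recommendations. Neither is a proportion improving on FBS, so the calculation neither supports the two-category outcome nor measures what it costs.

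**2. Assumed inputs.** The article gives none of these: SD of FBS change σ = 1.5 to 3 points; mean change μ = 0 to 1 point; baseline/follow-up correlation r = 0.5 to 0.8. Change is taken as a normal variable rounded to an integer.

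**3. Share unchanged.** Φ((0.5−μ)/σ) − Φ((−0.5−μ)/σ). For σ = 2, μ = 0.25: Φ(0.125) − Φ(−0.375) = 0.550 − 0.354 = 0.196. Over the whole range it is 12–26%.

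**4. Loss from dichotomising alone.** Relative efficiency is the information about a shift carried by the binary outcome, divided by that carried by the mean change. For improved versus not improved at σ = 2, μ = 0.25:
- proportion improved u = 1 − 0.550 = 0.450
- binary information = (φ(0.125)/2)² / (0.450×0.550) = 0.0392/0.2475 = 0.158
- information in the mean = 1/(4 + 1/12) = 0.245
- ratio = 0.158/0.245 = 0.65

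| Handling of unchanged scores | Relative efficiency | Loss |
|---|---|---|
| Counted as not improved | 0.63–0.66 | 34–37% |
| Counted as not worse | 0.46–0.64 | 36–54% |
| Dropped | 0.59–0.80 | 20–41% |

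The textbook benchmark for a median split is 2/π = 0.637, a loss of 36%.

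**5. Adding omission of baseline FBS.** The unadjusted change score has variance 2s²(1−r), with s the SD of FBS at a visit; ANCOVA has s²(1−r²). The efficiency of the change score relative to ANCOVA is therefore (1+r)/2. Multiplying by the improved-versus-not efficiencies:
- r = 0.5: factor 0.75, efficiency 0.48–0.50, loss 50–52%
- r = 0.6: factor 0.80, efficiency 0.51–0.53, loss 47–49%
- r = 0.8: factor 0.90, efficiency 0.57–0.59, loss 41–43%

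**6. In terms of power.** With 360 per arm, σ = 2, control mean change 0.25 and a true difference of 0.4 points, the standard error of the mean difference is √(2×4.083/360) = 0.151. Power is Φ(0.4/0.151 − 1.96) = 76%. Improved versus not compares 45.0% with 53.0% and has 57% power.

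**7. Simulation with the bounds at 0 and 15.** 360 per arm, mean about 9, SD 2–2.5, r 0.5–0.7, effect set for about 80% ANCOVA power. Ranges are over scenarios and repeated runs:

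| Analysis | Power |
|---|---|
| ANCOVA on follow-up FBS | 76–80% |
| Change-score test | 66–73% |
| Logistic, improved vs not, baseline FBS added | 54–58% |
| Logistic, improved vs worsened, unchanged dropped | 51–60% |
| Logistic, improved vs not, no baseline | 46–54% |

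Between 16% and 21% of simulated women were unchanged. Adding baseline FBS to the logistic model recovers only part of the gap.

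**The case against.** The best defence has four parts.

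- **This is a condensed article.** The rule for unchanged scores and the full covariate list may stand in an analysis plan that is not shown. That is fair, and their absence alone would not be a finding. But the logistic model and its two-category outcome are stated choices, and every rule for unchanged scores tried above loses information.
- **Baseline is not excluded.** A reader might infer that the analysis ignores the starting score. The text does not support that: the covariate list is open, and baseline enters through the change itself. Allocation is also randomised and stratified on factors that include BMI, blood pressure and smoking, which relate to three of the five FBS components. Leaving baseline out would cost mainly precision. This objection stands.
- **Direction of change is a legitimate summary.** The endpoint is worded as change, with no mean difference specified, and part of the hypothesis concerns improving. So the analysis is a coarse version of the endpoint, not an unrelated one. This stands too, but it does not give back the size of change or place the unchanged women.
- **A linear model is not perfect for a bounded ordinal score.** True, and a reason for an ordinal sensitivity analysis. The floor and ceiling affect the sign of change as well, so they do not favour dichotomising.

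**Conclusion.** The point holds. The primary FBS change is cut to two categories, with no place for unchanged scores and no mention of baseline FBS as a covariate. Under the assumed inputs, dichotomising alone costs about one third of the information, with a range of 20–54% over the rules for unchanged scores.

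A reader might conclude that half the information is lost outright. That does not follow from the documents. It needs baseline FBS to be left out as well, at r of about 0.5–0.6 and with ANCOVA as the comparator, or else unchanged women to be grouped with the improved when mean improvement is high. The article provides none of the quantities needed to settle this.

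A reader might also add the gap between 360 planned and 481 calculated per arm to the power loss. That is a separate matter and does not make this one larger, because the 45% and 54% are not FBS improvement rates.

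The choice should be changed before outcome data are examined by arm.

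**What to change.** **Primary analysis.** Model follow-up FBS on randomised arm, adjusted for baseline FBS and the randomisation stratification factors. Use linear ANCOVA, or a repeated-measures model covering 6 and 12 months. Analyse all randomised women as allocated, and report the adjusted mean difference with its 95% confidence interval.

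**Sensitivity analysis.** A proportional-odds model with the same terms, to respect the ordinal, bounded scale.

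**Secondary outcome.** Improvement by at least one point, with unchanged scores explicitly counted as not improved.

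**Cost.** No new data are needed, because the FBS is assessed at baseline and at both follow-up visits. The two-proportion sample-size statement would no longer match the primary analysis, so power should be restated for a mean FBS difference at 360 per arm with an assumed SD. As an illustration for the unadjusted change score, the difference detectable with 80% power is 2.80 × √(2(σ² + 1/12)/360): 0.32 points at σ = 1.5, 0.42 at σ = 2 and 0.63 at σ = 3. Baseline adjustment would reduce these.

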## Introduction

Cardiovascular (CV) disease in women requires more attention, more research, and swifter action. It remains the leading cause of death in women, reaching 41% in Europe, 16 times higher than breast cancer (3%), corresponding to one woman deceased every minute (1, 2). The immense economic and social burden of this devastating disease is evident, including physical and psychological consequences for women and their families. Although 80% of CV events can be prevented, the trend is projected to worsen, with an alarming increase in death rate in women, especially at young age (3, 4). Nearly 50% of women aged 40–54 years have atherosclerosis, with ≥2 arterial sites affected in 26% (5). Additionally, up to 40% of index cardiac events are fatal in women (6). Thus, identifying effective preventive and diagnostic strategies is of particular importance.

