## Hypothesis and objectives

Misperception of the burden of CV disease in women is a barrier to achieving reductions in RF and atherosclerosis in women. Risk awareness will induce heart-healthy living and facilitate early recognition of symptoms. Our hypothesis is that the use of VUS will increase women's awareness, producing a greater impact on lifestyle than standard risk assessment. We predict that compliance with lifestyle recommendations would be higher among women who have undergone an imaging study because they will have seen visual evidence of their own vessel wall damage or plaque presence. This prediction is supported by the success of large evidence-based strategies that have already been conducted to promote CV health in adults and children. For example, in the TANSNIP trial, authors found that in middle-aged asymptomatic adults, a lifestyle intervention was associated with a significant improvement in CV health and behavioral metrics (14). Similarly, primordial prevention strategies in children based on school educational interventions have been shown to improve health outcomes (15). However, specific studies exploring this approach in women are lacking (16). Additionally, the identification of accurate predictors of atherosclerosis in apparently low-risk women who already have disease will help estimate individual CV risk and implement risk-reduction programs. We also aim to analyze other woman specific factors such as hormonal changes, complications during pregnancy or psychosocial factors that can influence the development of atherosclerosis. Moreover, analysis of complex data relations in a high volume of data is not an easy task, and novel data processing techniques are required.

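### One 80/20 hold-out leaves about 72 or 144 women (depending on the unnamed target) to assess the exploratory prediction models; resampling all women with the outcome would be more precise

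*Protocol article*

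**What the plan says.** The Statistical analysis section of the protocol article adds machine learning to the regression of FBS improvement or worsening: "supervised and semi-supervised classifiers will be trained with 80% of the data to derive risk prediction models". The next sentence fixes the assessment: "Remaining 20% of the data will serve as a validation cohort". Neither sentence names the outcome of these models.

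Two other places bear on what that outcome could be and how many women would have it:

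- Hypothesis and objectives gives as an aim that "the identification of accurate predictors of atherosclerosis in apparently low-risk women who already have disease will help estimate individual CV risk". The Discussion, in its list of unique features, likewise looks for patterns associated with the presence of atherosclerosis.
- Study design and population describes a "case-control study that will include 720 women aged 40–70 years-old", randomized 1:1 as "360 with VUS vs. 360 age- and RF-matched controls without imaging". It adds: "Vascular imaging studies will be only performed at baseline". Table 1 shows no ultrasound at follow-up, so plaque status is never known in the control arm.

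**The concern.** A single hold-out uses each woman once, either for fitting or for testing. Four fifths of the women add nothing to the performance estimate, and the held-out fifth adds nothing to the model. In a cohort of this size the test set is small. It is smaller still if the label exists in only half the women. Semi-supervised training can make use of unlabelled women, but it does not add labelled women to test on.

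What is at stake is how the model's performance can be read. With a wide interval, a weak model and a useful one cannot be told apart. Because the 20% is called a validation cohort, a favourable estimate from one small subset of the same study could be taken for more than internal validation.

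**Working it through.** **The plan's own figure.** The article gives no size for the validation cohort beyond 20%. Its one computed sample size, 481, belongs to the two-proportion comparison and plays no part here.

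**Inputs from the article.** 720 women in total; 360 scanned; 20% held out.

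**Assumptions.** A true AUC of 0.75 (range 0.70 to 0.80) is not in the article. A case share of 45% is borrowed for illustration from the sample-size calculation, where it is a different quantity: the proportion developing disease without treatment. For plaque, the Introduction says "Nearly 50% of women aged 40–54 years have atherosclerosis", and the limitations paragraph of the Discussion warns that prevalence may be low. A range of 25% to 50% is therefore shown. Attrition is ignored.

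**Step 1: size of the hold-out.**

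- Target plaque: 0.20 × 360 = 72 women; at 45%, 32 cases and 40 non-cases.
- Target FBS change: 0.20 × 720 = 144 women; at 45%, 65 and 79.

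**Step 2: precision of the AUC (Hanley-McNeil).** With A the AUC, n1 cases and n0 non-cases:

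SE² = [A(1−A) + (n1−1)(Q1−A²) + (n0−1)(Q2−A²)] / (n1·n0), where Q1 = A/(2−A) and Q2 = 2A²/(1+A).

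At A = 0.75: Q1 = 0.6000, Q2 = 0.6429, A² = 0.5625. The three terms become 0.1875, (n1−1) × 0.0375 and (n0−1) × 0.0804.

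Worked for 72 women (32 and 40): (0.1875 + 31 × 0.0375 + 39 × 0.0804) / (32 × 40) = 4.484 / 1280 = 0.00350. So SE = 0.059 and the half-width is 1.96 × 0.059 = 0.116.

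| Women with held-out predictions | Cases / non-cases | SE | 95% half-width | Interval at AUC 0.75 |
|---|---|---|---|---|
| 72 (plaque, 20% hold-out) | 32 / 40 | 0.059 | 0.116 | 0.63 to 0.87 |
| 144 (FBS change, 20% hold-out) | 65 / 79 | 0.042 | 0.081 | 0.67 to 0.83 |
| 360 (plaque, all scanned women) | 162 / 198 | 0.026 | 0.051 | 0.70 to 0.80 |

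The last row treats cross-validated predictions as independent. They are not quite independent, so 0.05 is a best case.

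**Step 3: sensitivity to the assumptions.** With 72 women at AUC 0.75, the half-width is 0.142 at 25% prevalence (18 / 54) and 0.113 at 50% (36 / 36). Over AUC 0.70 to 0.80 and prevalence 25% to 50% it runs from 0.10 to 0.15. Over the same range it is about 0.07 to 0.11 with 144 women and about 0.05 to 0.07 with 360.

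**Step 4: a per-hospital check would be no better.** Equal recruitment at the 8 hospitals (an assumption) gives 360 / 8 = 45 scanned women each, about 20 cases and 25 non-cases at 45%. The same formula gives (0.1875 + 19 × 0.0375 + 24 × 0.0804) / 500 = 0.00566, so SE = 0.075 and a half-width of about 0.15.

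**The case against.** The strongest reply is that the article does not say the models predict plaque. The outcome modelled just before, in the same paragraph, is FBS improvement or worsening, which is planned in all 720 women. A reader might infer from the stated aims, and from the mention of semi-supervised methods, that the test set is 72. The text makes that plausible but does not establish it, so 72 and 144 must stand side by side.

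Other stronger readings also lack support:

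- **Omics overfitting.** The article plans methylation arrays and lipidomics but does not say that these variables enter the classifiers. The methylation data are to be used to estimate biological age.
- **A lucky random draw.** The article does not say that the split is random; it could be by hospital or by time.
- **A false claim of independence.** The 20% is never called external or independent.
- **No resampling at all.** Nothing rules out cross-validation within the 80% for tuning, and a condensed article may leave that to the full plan.
- **A main objective at risk.** No primary or secondary endpoint in Follow-up and end-points is a model's discrimination. The machine learning is introduced as additional work.

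What remains is that the 80/20 hold-out is stated, not merely left unspecified, and that it is an inefficient choice under either target.

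**Conclusion.** The concern holds as a minor improvement. The stated single hold-out would give an AUC known to about ±0.12 if the target is plaque (72 women), or ±0.08 if it is FBS change (144 women). The best case is about ±0.05 if all 360 scanned women contribute held-out predictions. These figures assume a true AUC of 0.75, 45% cases and no attrition. The ordering does not change over the ranges shown. That 72 women are too few is a judgement on precision: an interval of 0.63 to 0.87 covers both weak and good models. The randomized comparison on the FBS does not depend on any of this.

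**What to change.** In the Statistical analysis section, before any model is built:

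1. Name the target of each prediction model and its denominator: the 360 scanned women for plaque models, and the women with follow-up FBS for models of FBS change.
2. Replace the single 80/20 split with repeated nested cross-validation or bootstrap optimism correction on all women with the outcome, with any feature selection and tuning repeated inside each fold or bootstrap sample.
3. Call the result internal validation, not a validation cohort.
4. Optionally add leave-one-hospital-out performance, reported pooled only, because single-hospital estimates would be less precise than the hold-out being replaced.

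The cost is computing time and a few sentences; no new data, visits or participants are needed. The downside is that there is no longer a single validation-cohort figure to quote.
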